## Background

Postoperative delirium (POD) is an acute confusional state associated with changes in consciousness, arousal level and cognitive status characterized by inattention within 30 days after an operation 
[1] and occurs in 15 to 53% of older patients 
[1,2] particularly in those with hip fractures 
[1,3]. We have recently conducted a meta-analysis showing that delirium associated with hip fracture doubles the hazard ratio of death (HR 2.3 95% CI 1.4 to 3.9) 
[1]. Furthermore the development of delirium often initiates a cascade of events culminating in the loss of independence, poor functional recovery, and increased morbidity, as well as increases in length of hospital stay, discharges to nursing facilities, and healthcare costs 
[1-6].

The pathogenesis of delirium is poorly understood though Sanders has proposed that delirium can be considered as a ‘cognitive disintegration’ whereby the integrated neural function of the brain is broken down producing a varied range of symptoms focused on consciousness, arousal and memory 
[7]. Within the proposed framework various non-modifiable patient risk factors are hypothesized to contribute to reduced network connectivity (a surrogate for integration) at baseline, for example, age 
[7]. Modifiable risk factors (including inflammation and sedative drugs) act to further decrease network integration in the brain through altering the balance of neural transmission predominantly through increases in inhibitory tone mediated by γ-amino-butyric acid (GABA) signaling in the brain 
[7]. A prediction of this theory is that avoidance of GABAergic drugs, that include the majority of anesthetic (for example, sevoflurane or propofol) and sedative agents, would reduce the burden of postoperative and intensive care delirium.

In parallel, research showing multiple beneficial effects of the non-GABAergic anesthetic agent xenon has been published. As an inert, noble gas, xenon is not metabolized by the body but yet exerts myriad biological effects, the most notable being anesthesia and organ protection 
[8-18]. Xenon is thought to produce anesthesia through targeting either excitatory *N*-methyl-d-aspartate or two-pore-domain-potassium channels but not GABA_A_ receptors 
[8,9,13]. Xenon anesthesia is rapid onset, cadiostable and xenon is not thought to disturb autoregulation of organ blood flow 
[8,9,13]. Furthermore, xenon protects the brain, heart and kidney from diverse toxic insults including ischemia 

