### Statistical methods

The main analysis of the primary efficacy criterion will correspond to the primary objective of the study which is to evaluate the incidence of POD, diagnosed via CAM, in older patients undergoing hip fracture surgery under general anesthesia with xenon or sevoflurane, for a period of 4 days post-surgery. All data collected will be tabulated descriptively by group on the intention to treat (ITT) dataset (which will be composed of all randomized patients). The number of patients having being diagnosed POD with the CAM at least once throughout their study participation from visit 2 to visit 6 will be calculated in each group, and this number of patients will be divided by the total number of participating patients of the corresponding group. This ratio which represents the rate of POD diagnosed within 4 days post surgery will be compared between both groups, using the Pearson’s *χ*^2^ test and its calculation provided by the FREQ procedure of the current version of the SAS software (SAS, Cary, NC, USA), on the ITT dataset.

Additional analyses of the primary efficacy criterion as time elapsed between the onset of the maintenance period of the general anesthesia and the first POD diagnosis with the CAM post surgery (expressed in full number of started hours) will be tabulated by group, as both quantitative and categorical data, in the subgroup of patients for whom POD is diagnosed at least once within 4 days post surgery. Time to first POD diagnosis with the CAM post surgery will also be described globally by group, on the ITT dataset, using Kaplan-Meier estimates to display the probability of survival and of being diagnosed POD. Survival times will be censored at the time of the patients’ last contact (in the subgroup of patients for whom POD is never diagnosed within their trial participation post surgery) or at the time of the first POD diagnosis with the CAM (in the subgroup of patients for whom POD is diagnosed at least once within their trial participation post surgery). If relevant, times to first POD diagnosis with the CAM post surgery will be compared between both groups with the Log rank test.

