### Sample size calculation

We assume an expected rate of 30.0% of POD diagnosed with the CAM at least once within 4 days post surgery on sevoflurane, see Table
2[3,25-32]. We hypothesize a reduction of 50% to a rate of 15.0% of POD on xenon. The type I error is set to be α = 0.05 (two-sided conditions) and the power (1 - β) equals 0.80. Taking the above-mentioned facts into consideration, the sample size calculation results in 121 patients per group (the estimation is based on the two-group *χ*^2^ test of equal proportions). With an expected 5.0% dropout rate over 4 days post surgery, 256 patients will be randomized in this trial, that is, 128 patients in the xenon and 128 patients in the sevoflurane group. The sample size calculation was performed using nQuery Advisor® Version 6.01 (Statistical Solutions, Saugus, MA, USA). 

**Table 2 T2:** Incidence of postoperative delirium

**Author**	**Study type**	**Patients**	**Age (years)**	**Method**	**Incidence**	**Comments**
Marcantonio E, 2001 [26]	RCT	64	>65	CAM	50%	Total (n = 126)
Marcantonio E, 2002 [27]	PCS	122	>65	CAM	40%	Subanalysis of [25]
Marcantonio E, 2002 [28]	PCS	126	>65	CAM	41%	Subanalysis of [25]
Furlaneto M, 2006 [3]	PCS	106	>65	CAM	29.1%	
Zakriya K, 2002 [29]	PCS	168	>65	CAM	28%	
Zakriya K, 2004 [30]	PCS	92	>65	CAM	28%	
Sharma P, 2005 [31]	PCS	47	>56	CAM	36%	
Galanakis P 2001 [32]	PCS	37	>60	CAM	40.5%	

This table is an excerpt from studies assessing delirium with the CAM. Based on these data the power for this study has been calculated.

CAM = Confusion Assessment Method; PCS = prospective cohort study; RCT = randomized controlled trial.

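### As worded, the time-to-first-POD rule censors diagnosed and undiagnosed patients alike, so the Kaplan-Meier and log-rank analyses have no event

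*Protocol article*

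**What the plan says.** All of this is in the protocol article, Statistical methods, second paragraph, among the further analyses of the primary efficacy criterion.

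- Time to first POD is tabulated by group in patients with POD within 4 days. No censoring is involved.
- Time to first POD is also described on the intention-to-treat set, "using Kaplan-Meier estimates to display the probability of survival and of being diagnosed POD".
- The rule for patients without POD is: "Survival times will be censored at the time of the patients’ last contact (in the subgroup of patients for whom POD is never diagnosed" during their participation.
- The same sentence goes on for the other patients: "or at the time of the first POD diagnosis with the CAM (in the subgroup of patients for whom POD is diagnosed" at least once.
- The comparison is conditional: "If relevant, times to first POD diagnosis with the CAM post surgery will be compared between both groups with the Log rank test".

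No other sentence in the article defines first POD as an uncensored event. Under Objectives, determining the time to first POD is a secondary objective, with no 4-day limit.

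**The concern.** In a time-to-event analysis, a patient who reaches the endpoint contributes an event at that time, and a patient who leaves observation without it is censored. Here both kinds of patient are censored. The two subgroups, never diagnosed and diagnosed at least once, exclude each other and leave nobody out, so no patient in the intention-to-treat set can have an event. That contradicts the sentence just before, which has the curves show the probability of a POD diagnosis.

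What is at stake is the only planned time analysis on all randomized patients, and the only between-group comparison of times. Followed to the letter, neither gives a usable result.

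Two smaller matters lie in the same sentences. The censoring time for undiagnosed patients is last contact, which can fall after the last CAM. And the time window is unclear: the analysis is grouped under a 4-day criterion, yet the censoring rule speaks of the whole trial participation.

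**Working it through.** **Inputs.** From Sample size calculation: POD 30.0% on sevoflurane ("We assume an expected rate of 30.0% of POD diagnosed with the CAM at least once within 4 days post surgery on sevoflurane"), 15.0% on xenon, two-sided α 0.05, power 0.80, 121 per group before and 128 per group after 5.0% dropout. From Statistical methods: the censoring rule. From Table 1: the CAM schedule.

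**1. The plan's own figure.** With mean proportion 0.225,

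n = [1.96·√(2 × 0.225 × 0.775) + 0.8416·√(0.30 × 0.70 + 0.15 × 0.85)]² / 0.15² = (1.1575 + 0.4889)² / 0.0225 = 120.5, rounded up to 121.

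121 / 0.95 = 127.4, rounded up to 128 per group, 256 in all. The figure reproduces and does not depend on the censoring rule.

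**2. The rule as written.** Every event indicator is 0.

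- Kaplan-Meier: S(t) = ∏(1 − dⱼ/nⱼ). With every dⱼ = 0, S(t) = 1 throughout and the estimated probability of POD is 0 in both arms.
- Log-rank: the expected count in an arm at time j is dⱼ·n₁ⱼ/nⱼ = 0, and its variance is also proportional to dⱼ, so 0. The statistic is 0/0, undefined.

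On an illustrative data set of 256 patients (38 with POD on sevoflurane, 19 on xenon, arbitrary times), this coding gave an empty curve, and the log-rank routine stopped on a singular matrix. With POD coded as the event, the same data gave a normal result, and the sevoflurane curve ended at 90/128 = 0.703.

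**3. Events available once POD is the event.**

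- All randomized: 128 × 0.30 + 128 × 0.15 = 38.4 + 19.2 = 57.6, about 58.
- Evaluable only: 121 × 0.30 + 121 × 0.15 = 36.3 + 18.15 = 54.45, about 54.

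These are 4-day planning rates. First diagnoses after day 4 would add to them if the whole stay is meant.

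**4. Is the repaired analysis workable?** Assume proportional hazards, which the article does not state. Then HR = ln(0.85)/ln(0.70) = 0.456. Schoenfeld's formula gives 4 × (1.96 + 0.8416)² / (ln 0.456)² = 51 events for 80% power. With 54 to 58 events the power is about 82% to 85%. So the wording defeats an analysis that would otherwise be informative.

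**5. Censoring time.** Table 1 schedules CAM at selection and at visits 2 to 7, and none at visit 8 (study end), where adverse events and concomitant medication are still recorded. Last contact can therefore be later than the last time POD could have been detected.

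**6. Window.** Evaluation criteria limits the primary criterion to 4 days. The censoring sentence refers to trial participation, which under Follow-up visits runs to discharge or at most 28 days. The text does not reconcile the two.

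**The case against.** The strongest reply is that the intent is plain. The preceding sentence names POD diagnosis as what the curves show, and the rule gives each subgroup the right kind of end time and merely uses censored loosely. A programmer would probably code it correctly, and a flat curve would expose the error at the first run. That stands and limits the severity. It does not make the sentence right. Nor is this a detail left to the analysis plan: the article states a rule, and the rule is wrong.

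A reader might infer more, and the article does not support it:

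- **That the secondary objective on time to first POD cannot be answered.** The 4-day tabulation in patients with POD involves no censoring and still describes it.
- **That censoring at discharge is shown to be informative**, because the Background links delirium to "increases in length of hospital stay, discharges to nursing facilities, and healthcare costs". That concerns patients who already have the event. It does not show that undiagnosed patients are censored in a way related to their POD risk.
- **That follow-up must stop at day 4.** The Kaplan-Meier description is meant to be global, and the objective has no 4-day limit. The Discussion does say that delirium after 4 days is unlikely to be due to the anesthetic technique. That is a reason to state the window, not proof that the longer one is wrong.
- **That competing-risk curves or an unconditional log-rank test are required.** These are reasonable preferences. The criterion behind the conditional test may stand in the analysis plan, which is not shown.

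**Conclusion.** Wrong as written. Read literally, the Kaplan-Meier and log-rank analyses of time to first POD contain 0 events, against about 58 expected by day 4 among 256 randomized patients (about 54 among 242 evaluable). The zero follows from the text alone. The expected counts rest on the article's planning rates of 30% and 15%.

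Severity is minor to moderate. The analysis is additional, its intent can be inferred, and a wrong result is unlikely to pass unnoticed. A reader might take the flaw to reach the trial's main result. It does not: the Pearson chi-square test uses the proportion diagnosed from visit 2 to visit 6 and needs no censoring rule, and the sample size is built on that test.

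**What to change.** Replace the censoring sentence with one to this effect: the first positive CAM after surgery is the event, at its time of diagnosis; only patients never diagnosed are censored, at their last CAM evaluation.

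Add a sentence saying whether this analysis covers the 4 days of the primary criterion or the whole stay up to discharge or day 28. If it covers 4 days, the last CAM counted is at visit 6.

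The cost is wording in the protocol and, if it repeats the rule, in the analysis plan. No new data, visits or patients are needed, and the primary analysis and sample size stay as they are.

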### Sample size calculation

We assume an expected rate of 30.0% of POD diagnosed with the CAM at least once within 4 days post surgery on sevoflurane, see Table
2[3,25-32]. We hypothesize a reduction of 50% to a rate of 15.0% of POD on xenon. The type I error is set to be α = 0.05 (two-sided conditions) and the power (1 - β) equals 0.80. Taking the above-mentioned facts into consideration, the sample size calculation results in 121 patients per group (the estimation is based on the two-group *χ*^2^ test of equal proportions). With an expected 5.0% dropout rate over 4 days post surgery, 256 patients will be randomized in this trial, that is, 128 patients in the xenon and 128 patients in the sevoflurane group. The sample size calculation was performed using nQuery Advisor® Version 6.01 (Statistical Solutions, Saugus, MA, USA). 

**Table 2 T2:** Incidence of postoperative delirium

**Author**	**Study type**	**Patients**	**Age (years)**	**Method**	**Incidence**	**Comments**
Marcantonio E, 2001 [26]	RCT	64	>65	CAM	50%	Total (n = 126)
Marcantonio E, 2002 [27]	PCS	122	>65	CAM	40%	Subanalysis of [25]
Marcantonio E, 2002 [28]	PCS	126	>65	CAM	41%	Subanalysis of [25]
Furlaneto M, 2006 [3]	PCS	106	>65	CAM	29.1%	
Zakriya K, 2002 [29]	PCS	168	>65	CAM	28%	
Zakriya K, 2004 [30]	PCS	92	>65	CAM	28%	
Sharma P, 2005 [31]	PCS	47	>56	CAM	36%	
Galanakis P 2001 [32]	PCS	37	>60	CAM	40.5%	

This table is an excerpt from studies assessing delirium with the CAM. Based on these data the power for this study has been calculated.

CAM = Confusion Assessment Method; PCS = prospective cohort study; RCT = randomized controlled trial.

### Study monitoring, audit and inspection

The study will be monitored regularly (visits and telephone monitoring) by Air Liquide Santé International personnel or any company appointed by the latter. During the monitoring visits, the clinical research associate (CRA) will verify the consistency of the data recorded on the case report forms with the source documents (patient’s medical file, nurse’s chart, and so on). The CRA will also verify the management of therapeutic batches, the presence and completeness of the investigator file and general study compliance with good clinical practice guidelines. An on-site audit may be requested and performed by the sponsor or designee personnel at any time.

## Discussion

To date, 121 patients have been randomized (July 2012) in this phase 2 study. Inclusion of patients is approximately 50% slower than expected. For this reason the recruitment period of this trial was extended from the end of 2012 to the end of 2013. Furthermore, three new sites will be selected. Approximately two out of ten screened patients have been included so far. This is due to the strict inclusion and exclusion criteria especially cognitive impairment (MMSE < 24), dementia or depression. However, in this phase 2 study we need to keep above-mentioned inclusion and exclusion criteria to be able to show efficacy. We are awaiting the results of this trial to anticipate a phase 3/4 trial, which would have different inclusion and exclusion criteria including patients with reduced capacity. The primary objective of this study is to evaluate the incidence of postoperative delirium, diagnosed with the CAM, in older patients undergoing hip fracture surgery under general anesthesia with xenon or sevoflurane, for a period of 4 days post surgery. Postoperative delirium occurs predominantly in the first 4 days following hip fracture surgery 
[25], during this period it declines rapidly (peak on day 1, and on day 4). Thereafter it plateaus. Delirium occurring after 4 days is unlikely to be due to the anesthetic technique; therefore we only included the first 4 days for the primary endpoint. Furthermore the CAM is validated for use in older patients 
[33]. A big effort was made to design this study in s double blinded way and to keep the non-blinded bias as low as possible. Throughout the study, there will be two teams of physicians involved in the patient’s follow-up. Physician 1 will perform the visits, which include selection of patients, follow-up visits and study end visit. Physician 1 will be kept blinded regarding the natures and doses of all study drugs administered throughout the study. Physician 2 will perform randomization and surgical procedure under general anesthesia. However, physician 2 who is performing anesthesia is not blinded due to technical reasons applying xenon anesthesia. However, the bias of physician 2, who is aware of the randomization allocation, is kept minimal. Physician 2 is not involved in the assessment of the outcome parameters. Furthermore, the case report forms are strictly separated and kept locked so physician 2 is not able to access the case report forms of physician 1 and vice versa.

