**Figure 1 F1:**
[figure not shown]
**Study flow chart of the Hip Fracture Surgery in Elderly Patients (HIPELD) study.** V = visit; d = day; hrs = hours, GA = general anesthesia.

Physician 1 will perform visits 0, 2, 3, 4, 5, 6, 7 and 8, which includes selection of patients, follow-up visits and study end visit. Physician 1 will be kept blinded regarding the natures and doses of all study drugs administered throughout the study (Table
1 and Figure
1).

**Table 1 T1:** Study evaluations

	**Visit 0**^**a**^**(selection)**	**Visit 1**^**b**^ (**GA)**	**Visit 2**^**a**^**(3 h post GA)**	**Visit 3**^**a**^**(day 1)**		**Visit 4**^**a**^ (**day 2)**		**Visit 5**^**a**^ (**day 3)**		**Visit 6**^**a**^ (**day 4)**		**Visit 7**^**a**^ (**day 5 to D)**		**Visit 8**^**a**^ (**study end)**
				**A**	**B**	**A**	**B**	**A**	**B**	**A**	**B**	**A**	**B**	
Signed informed consent	X													
Selection criteria	X													
Demographic data	X													
Vital signs	X	X	X	X		X		X		X		X		
Medical and surgical history	X													
Concomitant diseases	X													
Concomitant medication	X	X	X	X	X	X	X	X	X	X	X	X	X	X
MMSE evaluation	X													
Randomization			X											
General anesthesia			X											
Blood sample	X			X		X		X		X		According to investigator’s judgment		
CAM evaluation	X		X	X	X	X	X	X	X	X	X	X	X	
Pain VAS evaluation	X	X	X	X		X		X		X				
Verbal Rating Scale for Nausea		X	X	X										
SOFA	X			X		X		X		X		According to investigator’s judgment		
Recovery parameters		X												
Adverse events		X	X	X	X	X	X	X	X	X	X	X	X	X

A represents 10:00 am ± 30 minutes; B represents 6:00 pm ± 30 minutes; day 5 to D is post-surgery day 5 until discharge from hospital (or at maximum 28 days post surgery), or withdrawal from the study.

^a^Physician 1; ^b^Physician 2.

CAM = Confusion Assessment Method; GA = general anesthesia; MMSE = Mini-Mental State Examination; SOFA = Sequential Organ Failure Assessment; VAS = visual analog scale.

Physician 2 will perform visit 1, which includes randomization and surgical procedure under general anesthesia.

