### Wake up

At 10 minutes before the expected end of all surgical procedures, the inhaled anesthetic agents will be reduced to 0.5 MAC. After the effective skin closure, the Train of Four (TOF) test will be performed to exclude existing neuromuscular relaxation. From this timepoint, adequate spontaneous ventilation has to be ensured and end-tidal carbon dioxide level is allowed to increase up to 50 mmHg. Recovery parameters, namely time to open eyes, time to react on verbal command, time to extubation and time to spatial orientation, are to be recorded.

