### Evaluation criteria

The primary efficacy criterion is POD diagnosed via CAM at least once within 4 days post surgery.

The secondary efficacy criteria include: (1) POD diagnosed with the CAM from day 5 post surgery to discharge from hospital; (2) SOFA from day 1 to day 4 post surgery; (3) recovery parameters; (4) economic parameters, which are addressed to evaluate the economical impact of POD in the postoperative period from the hospital perspective; (5) safety: adverse events and serious adverse events, and laboratory parameters.

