### Safety evaluations

All adverse events (AEs) occurring during the whole study period will be recorded by the investigators. Physician 1 will record all AEs apart from those occurring on the day of the surgery, between the time of admission of the patients in the operating room to the time of discharge of the patients from the PACU. The information recorded in the case report forms for each AE experienced by the patients throughout their whole study period will include the nature of the events, their onset date and time, their end date and time, their severity, the corrective treatment(s) started if applicable, the outcome of the events and their relationship to the investigational inhaled gas and to the intravenous line applied separately as assessed by the investigator who records the AE. Physician 1 will record the relationships of each AE described to the investigational inhaled gas and to the intravenous line applied separately without knowing the nature of the study drugs administered.

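### The Discussion says the unblinded physician 2 assesses no outcome parameters, but other sections give that physician recovery parameters, economic parameters and adverse events from operating-room admission to PACU discharge

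*Protocol article*

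**What the plan says.** Two physician teams follow each patient. Physician 1 is blinded and performs visit 0 and visits 2 to 8. For the other team, the text with Table 1 states: "Physician 2 will perform visit 1, which includes randomization and surgical procedure under general anesthesia". The Discussion concedes that "physician 2 who is performing anesthesia is not blinded due to technical reasons applying xenon anesthesia", and then gives as a reason why the resulting bias is small: "Physician 2 is not involved in the assessment of the outcome parameters". That sentence is not limited to delirium or to any other named outcome.

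The Evaluation criteria section lists five secondary efficacy criteria. Among them are "3) recovery parameters", economic parameters as the fourth, and "5) safety: adverse events and serious adverse events, and laboratory parameters".

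The Wake up section says of the recovery parameters: "time to open eyes, time to react on verbal command, time to extubation and time to spatial orientation, are to be recorded". It does not say by whom. The Economic parameters section names physician 2 as recorder of theatre times, anesthesia and surgery times (time of extubation included), drug consumption and type of operation. On adverse events, the Safety evaluations section says: "Physician 1 will record all AEs apart from those occurring on the day of the surgery, between the time of admission" to the operating room and discharge from the PACU. The same section has the recording investigator judge the event's relationship to the inhaled gas. It says physician 1 does this without knowing the study drugs, and gives no such assurance for the other recorder.

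**The concern.** The sentence in the Discussion describes a protection against bias, and readers will rely on it when they weigh the secondary results. If the unblinded physician in fact supplies some of those results, the protection is absent where it is claimed.

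The exposure differs by outcome. Times to verbal response and to spatial orientation depend on when and how the observer prompts the patient, so knowledge of the allocation can shift them. Physician 2 also uses neuromuscular monitoring to decide when anesthesia is discontinued (section on the surgical procedure), and so influences the event being timed as well as observing it. Judging whether an AE is related to the inhaled gas is a matter of opinion, and the window concerned covers the whole of the gas exposure. Clock times and drug consumption leave less room for judgement, but by the plan's own list they are still outcome data.

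**Working it through.** No figure is at stake. The check is to ask, for each listed criterion, who collects the data and whether that person knows the allocation.

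| Criterion (Evaluation criteria) | Who collects it | Basis | Blinded? |
|---|---|---|---|
| Primary: CAM, visits 2 to 6 | Physician 1 | Stated: visit assignment, Table 1, Statistical methods | Yes |
| (1) CAM from day 5 to discharge | Physician 1 | Stated: visit 7 | Yes |
| (2) SOFA, days 1 to 4 | Physician 1 | Stated: visits 3 to 6 | Yes |
| (3) Recovery parameters | Physician 2 | Inferred: marked in Table 1 only at visit 1; Wake up names no recorder | No |
| (4) Economic parameters, as listed in that section | Physician 2 | Stated by name | No |
| (5) AEs, operating-room admission to PACU discharge, day of surgery | Physician 2 | Inferred: excluded from physician 1, and only two teams exist; Table 1 marks AEs at visit 1 | No |
| (5) AEs at all other times | Physician 1 | Stated | Yes |

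For criterion (3), the table is not the only support. The four times are measured at emergence, whereas physician 1's first postoperative visit is 3 h after anesthesia. The Economic parameters section also gives physician 2 by name the recording of the time of extubation, which underlies one of the four recovery times. This matters because Table 1, as read from the PDF, places the marks for randomization and general anesthesia under visit 2, against the text that assigns both to visit 1. Its visit 1 and visit 2 columns should therefore not carry the argument alone.

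For criterion (5), the start of the window needs care. It opens at admission to the operating room on the day of surgery, so events before that stay with physician 1.

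Count: physician 2 contributes to criteria (3), (4) and (5), that is, 3 of 5. Criterion (3) appears to be wholly unblinded, (4) is unblinded for the items listed, and (5) is unblinded for one window. The Discussion sentence allows for none.

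**The case against.** The strongest defence is context. The Discussion deals with CAM and the four-day endpoint just before it turns to blinding, so the outcome parameters could mean the delirium outcome. On that reading the sentence is true. The article also conceals little: Table 1 labels each visit by physician, the AE window is set out, and physician 2's knowledge of the allocation is admitted. This is a fair account of how the sentence came to be written. It does not rescue the sentence, which carries no such limit and is offered as the safeguard for the trial as a whole.

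A reader might infer several stronger points that the document does not support:

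- **That the trial is falsely presented as double blind.** The design is formally called blinded. The Discussion speaks of an effort toward double blinding and discloses its limit in the same paragraph.
- **That a confirmatory claim on recovery parameters is undermined.** The Statistical methods section announces descriptive tabulation of all data and specifies between-group tests only for delirium.
- **That blinded and unblinded causality judgements will be pooled.** The article does not say how relatedness will be tabulated, and such layouts are commonly left to an analysis plan.
- **That the pain and nausea scores at visit 1 add to the conflict.** They are not among the listed criteria, and patients rate them themselves.

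It also stands that no sentence names physician 2 as recorder of eye opening, verbal response or orientation, or of the AEs in the window. Those two attributions are inferences, though no other recorder is available in the design as described.

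**Conclusion.** The Discussion statement is wrong as written. It holds for CAM, SOFA and AEs outside the window from operating-room admission to PACU discharge. It does not hold for the economic parameters recorded by physician 2, which is explicit, or for recovery parameters and AEs within that window, which follows by inference from the visit assignments and from what is excluded from physician 1.

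A reader might take this as a threat to the main result. It is not: the primary endpoint rests on CAM assessments by the blinded physician 1. The consequence is confined to how much weight the secondary recovery results and the perioperative causality judgements can bear. The documents give no basis for putting a size on any resulting bias, so none is claimed.

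The conclusion assumes that there is no third, blinded recorder in the operating room or PACU. The article describes only two teams.

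**What to change.** 1. In the Discussion, limit the statement on physician 2 to CAM, SOFA and AEs outside the window from operating-room admission to PACU discharge on the day of surgery.
2. State that recovery parameters, the economic parameters recorded by physician 2, and AEs within that window (with their causality) are assessed or recorded unblinded. Name the recorder in the Wake up and Safety evaluations sections, so that it need not be inferred.
3. Interpret recovery parameters as open-label observations.
4. Tabulate AE relatedness separately for the unblinded window and for the remaining, blinded period.

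The cost is a text correction, one extra split of the AE relatedness tables and a weaker blinding claim for these secondary outcomes. Sample size, treatment and the primary analysis do not change. With 121 of 256 patients randomized at the time of writing, the change can be made before the data are analyzed.
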